#### **5.1.1 Pilot Stage**

The purpose of the Pilot Stage is to ensure the safety of the surgical technique and study drug administration and, if necessary, optimise these prior to initiating the Primary Study Stage. Six subjects with PD of moderate severity will be randomised in a 2:1 allocation (total of 4 subjects receiving active GDNF and 2 subjects receiving placebo) to receive infusions of GDNF or placebo every 4 weeks in a double-blind fashion for 9 months (10 infusions; last infusion at Week 36). A safety review of these 6 subjects will be performed by both the independent Data Monitoring Committee (DMC) and the Medicines and Healthcare Products Regulatory Agency (MHRA) after the last pilot subject has completed 3 months of treatment. While the Pilot Stage is primarily aimed at confirming the safety of the study treatments and procedures and meeting regulatory requirements as articulated by the MHRA, it also serves to potentially optimise options for handling infusions in subjects allowing minor modifications of procedures in response to any surgical, technical, infusion, imaging or logistical issues that may be identified. Subjects randomised in the Pilot Stage will be analysed together with the subjects randomised in the Primary Study Stage as part of the safety and supplementary efficacy analyses but will not be included in the primary efficacy analysis.

**Figure 7 Study Schema**[figure not shown]

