### **5.2.5 Safety Endpoints**

- Frequency of device-related adverse events (AEs) during the study period
- Frequency of treatment-emergent AEs (all treatment-emergent AEs and treatment-emergent AEs related to study drug) during the study period.
- Frequency of dyskinesias, falls, adverse changes in mood, and impulsivity reported as treatment-emergent AEs during the study period (AEs of special interest).
- Change from baseline in the Questionnaire for Impulsive-Compulsive Disorders in Parkinson's Disease (QUIP) every 8 weeks.
- Change from baseline in the Montreal Cognitive Assessment (MoCA) after 9 months of double-blind treatment.
- Change from baseline in the Mattis Dementia Rating Scale (MDRS) after 9 months of double-blind treatment.
- Adverse changes in MRI findings as captured by AE reporting.
- Frequency of subjects with anti-GDNF antibodies during the study.
- Results of routine laboratory blood tests (haematology, serum chemistry) and urinalysis performed at baseline and at intervals during the trial.

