***Pilot Stage subjects:*** The infusion of blinded study drug will be performed in the 3T MRI suite with real-time MR imaging. Rapid acquisition T2-weighted and FLAIR MRI scans will be performed at approximately 20 minute intervals. Real-time MRI scans will be assessed by the PI, Study Neurosurgeon or appropriately experienced designee. Real-time imaging will facilitate immediate cessation of infusions via one or more catheters if any of the following criteria are met:

1. Intraputamenal haemorrhage or post-surgical fluid collection is identified
2. The catheter is blocked
3. There is significant reflux of infusate out of the putamen without evidence of intrapatamenal distribution.

Final T2-weighted and FLAIR 3T MRI scans will be completed within 2 hours of the infusion.

Subjects will be carefully observed for safety during and after study drug administration. During administration, whilst in the scanner, HR, RR and oxygen saturation will be monitored continuously, and systolic and diastolic BP will be collected every 15 minutes. Both seated and standing systolic and diastolic BP and HR will be assessed within 30 minutes after the end of the infusion. A brief neurological

screen (Glasgow Coma Scale) will also be done before infusion, 30 minutes into the infusion, and after completion of the infusion.

Subjects will remain at the facility for safety observation for at least 22 hours (i.e., including an overnight stay) after completing study drug administration.

**Primary Study Stage subjects:** Subjects will be carefully observed for safety during and after study drug administration. During administration, seated vital signs (systolic and diastolic BP, HR and RR) will be collected every 15 minutes, and both seated and standing systolic and diastolic BP and HR will be assessed within 30 minutes after the end of the infusion. A brief neurological screen (Glasgow Coma Scale) will also be done before infusion, 30 minutes into the infusion, and after completion of the infusion.

Subjects will remain at the facility for safety observation for at least 4 to 6 hours after completing study drug administration.

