#### **5.6.4 Laboratory and Other Assessments**

The following laboratory procedures will be performed at Weeks 4, 16, and 28:

- Clinical laboratory tests, including haematology (haematocrit, haemoglobin, MCH, MCHC, MCV, platelet count, RBC, WBC count and WBC differential [basophils, eosinophils, lymphocytes, monocytes and neutrophils]), serum chemistry (albumin, alkaline phosphatase, ALT, creatinine, eGFR, glucose, potassium, sodium, total bilirubin and urea) and urinalysis (colour, appearance, pH, glucose, ketones and nitrite; microscopy only required if indicated to follow up abnormal findings). A pregnancy test will be performed for all women of childbearing potential.
- Blood samples for anti-GDNF antibodies and plasma GDNF levels. The samples will be stored at -70°C until central analysis after all subjects have completed the study.

Subjects will undergo NMSS (Section 5.7.1.5) and RT (Section 5.7.2.4.3) assessments at Weeks 12 and 24.

In subjects randomised in the Pilot Stage, T2-weighted and FLAIR 3T MRI will be completed within 2 hours of completion of the infusions at all post-baseline treatments. In Primary Study Stage subjects, no interim T2-weighted or FLAIR MRI monitoring will be done unless clinically mandated. However, Primary Study Stage subjects will receive another gadolinium contrast-containing test infusion of diluent, followed both by T1-weighted and by T2-weighted and FLAIR MRI scans, at any time within a 2-week window around Week 40.

In subjects randomised in the Pilot Stage, PET will be performed at Week 12. All subjects will undergo PET scanning at any time in the two weeks prior to Week 40.

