## 8.7 Inclusion in Analysis

The primary analysis will be conducted after all Primary Study Stage subjects have reached the 9-month endpoint.

The primary analysis population will include all subjects randomised to the study in the Primary Study Stage of the study. The primary analysis will follow the ITT principle, with all subjects randomised in the Primary Study Stage included and grouped according to randomised treatment (regardless of treatment received). Subjects randomised in the Pilot Stage will not be included in the ITT population for the primary analysis as the treatment parameters may be altered during this phase.

In addition, efficacy analyses will be repeated on the ITT Overall Population comprising all randomised Primary Stage subjects and all randomised Pilot Stage subjects and on the Per Protocol Population, comprising all subjects treated in the study (i.e., including subjects randomised in the Pilot Stage) and without major protocol violations. Misrandomisations constitute major protocol violations.

The Safety Primary Population will comprise all Primary Study Stage subjects who received at least one dose of study medication, with subjects grouped according to treatment actually received. All safety analyses will be performed on the Safety Primary Population. More limited analyses will be performed for the Safety Overall Population comprising all subjects (both Pilot and Primary Study Stage) who received at least one dose of study medication, with subjects grouped by treatment actually received. Safety data for Pilot Stage subjects will be provided and evaluated via individual data listings. Pre-treatment AEs will be analysed in the Safety Enrolled Population comprising all enrolled subjects (Primary Study Stage and Pilot Stage subjects combined).

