**Table 2 Schedule of Events (Double-Blind Treatment)**

| Procedure/Assessments                                   | Week           |   |                |                |                 |    |                 |    |                 |    |                 |
|---------------------------------------------------------|----------------|---|----------------|----------------|-----------------|----|-----------------|----|-----------------|----|-----------------|
|                                                         | 0 c | 4 | 8 c | 12             | 16 c | 20 | 24 c | 28 | 32 c | 36 | 40 c |
| MRI (Pilot subjects) a                       | X              | X | X              | X              | X               | X  | X               | X  | X               | X  |                 |
| MRI (Primary Study Stage subjects) b         |                |   |                |                |                 |    |                 |    |                 |    | X               |
| PET                                                     | X d |   |                | X e |                 |    |                 |    |                 |    | X f  |
| Vital signs g                                | X              | X | X              | X              | X               | X  | X               | X  | X               | X  | X               |
| Weight and height                                       | X              |   | X              |                | X               |    | X               |    | X               |    | X               |
| Physical examination h                       |                |   |                |                |                 |    |                 |    |                 |    | X               |
| ECG                                                     |                |   |                |                |                 |    |                 |    |                 |    | X               |
| Laboratory assessment i                      |                | X |                |                | X               |    |                 | X  |                 |    | X               |
| Anti-GDNF antibody levels and GDNF plasma concentration |                | X |                |                | X               |    |                 | X  |                 |    | X               |

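### Safety Overall is grouped by treatment only, so the 4:2 Pilot allocation and the 10-versus-1 MRI schedule tilt pooled MRI-detected AE frequencies slightly towards GDNF

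*Protocol*

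**What the plan says.** Section 8.7 defines three safety sets. On the main one it says "All safety analyses will be performed on the Safety Primary Population". On the combined one it says "More limited analyses will be performed for the Safety Overall Population comprising all subjects (both Pilot and Primary Study Stage") who had at least one dose, grouped by the treatment actually received; stage is not part of the grouping. It then adds "Safety data for Pilot Stage subjects will be provided and evaluated via individual data listings". Section 5.1.1 also says that Pilot subjects are analysed together with Primary subjects in the safety analyses, and section 4.2 sets a safety objective covering both the pilot cohort and the whole study population.

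The stages differ as follows.

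- **Allocation.** Pilot subjects are "randomised in a 2:1 allocation (total of 4 subjects receiving active GDNF and 2 subjects receiving placebo") (5.1.1). Primary subjects are allocated 1:1 in blocks of 6 (5.5.4).
- **Scheduled MRI after first dose.** The row "MRI (Pilot subjects") in Appendix A, Table 2 is marked at every infusion from Week 0 to Week 36, with real-time imaging as well at Week 0. For the other stage, section 5.6.4 says "In Primary Study Stage subjects, no interim T2-weighted or FLAIR MRI monitoring will be done unless clinically mandated"; its one scheduled post-dose scan is at Week 40, when Pilot subjects have none.
- **Post-infusion observation.** At Week 0 in the Pilot Stage, "Subjects will remain at the facility for safety observation for at least 22 hours" (5.6.1), against at least 4 to 6 hours in the Primary Study Stage.

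Section 5.2.5 lists among the safety endpoints "Adverse changes in MRI findings as captured by AE reporting". Section 8.1 makes all safety reporting descriptive, by treatment group.

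**The concern.** If more scanning finds more events, Pilot subjects will have a higher frequency of MRI-detected AEs than Primary subjects whatever they receive. Within a stage this is harmless, because both arms follow the same schedule. It becomes a between-arm difference only because the allocation ratio also changes between stages: the heavily scanned subjects are a larger share of the pooled GDNF group than of the pooled placebo group. A table grouped by treatment alone therefore compares two different mixtures of scan schedules.

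At stake is a side-by-side column of percentages in a neurosurgical Phase II trial, where a reader could take a schedule effect for a drug effect. No test is needed for a crude percentage to mislead. The pooled figure also describes no single schedule of looking, so it is hard to read as an incidence.

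**Working it through.** **Inputs**

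- Pilot: 4 GDNF, 2 placebo (5.1.1).
- Primary: 36 subjects at 1:1 in blocks of 6 (5.1.2, 5.5.4). Six complete blocks give 18 + 18; this split, and all 42 subjects being dosed as allocated, are assumptions.
- Scheduled scans after the first dose (Table 2): Pilot 10, Primary 1. Clinically mandated extra scans in the Primary Study Stage are not counted.
- Detection rates: not given in the protocol, so a range is used.

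The protocol states no figure for the Safety Overall comparison, so there is none to reproduce. Its subject counts agree: 4 + 2 + 18 + 18 = 42.

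**Step 1. Mixture weights.** The Pilot share is 4/22 = 18.2% of GDNF and 2/20 = 10.0% of placebo. The difference is 0.1818 − 0.1000 = 0.0818.

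**Step 2. Scheduled scans per subject.** GDNF (4×10 + 18×1)/22 = 58/22 = 2.64. Placebo (2×10 + 18×1)/20 = 38/20 = 1.90.

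**Step 3. Expected difference with no drug effect.** Let the subject-level frequency be q_pilot in the Pilot Stage and q_primary in the Primary Study Stage, equal in both arms. Each pooled arm has w × q_pilot + (1 − w) × q_primary, so

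difference = 0.0818 × (q_pilot − q_primary).

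The ceiling is 8.2 points, when every Pilot subject and no Primary subject has a finding. If q_pilot = q_primary, the difference is zero.

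**Step 4. A range for detection.** Assume probability p per scan, equal in both arms and independent between scans. Then q_pilot = 1 − (1 − p)^10 and q_primary = p.

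| p per scan | Pilot | Primary | Pooled GDNF | Pooled placebo | Difference | Ratio |
|---|---|---|---|---|---|---|
| 2% | 18.3% | 2% | 5.0% | 3.6% | 1.3 points | 1.37 |
| 5% | 40.1% | 5% | 11.4% | 8.5% | 2.9 points | 1.34 |
| 10% | 65.1% | 10% | 20.0% | 15.5% | 4.5 points | 1.29 |

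Differences come from unrounded rates; subtracting the rounded percentages in the first row would give 1.4. In GDNF subjects the shift is 22 × 0.0133 = 0.3, 22 × 0.0287 = 0.6 and 22 × 0.0451 = 1.0. At the ceiling it is 22 × 0.0818 = 1.8.

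**Step 5. When the two stages can detect different things.** Pilot scans follow study-drug infusion within 2 hours; the Primary Week 40 scan follows a diluent test infusion (Table 2, notes a and b). A transient change after study drug could be seen on a scheduled scan only in the Pilot Stage. As q_primary approaches zero, the ratio approaches 0.1818/0.1000 = 1.82.

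**Step 6. Direction in a single trial.** Exact calculation under no drug effect gives a probability of 0.57 (p = 5%) and 0.65 (p = 10%) that the observed GDNF frequency exceeds placebo. A two-sided Fisher test on the pooled table, if one were run, would reject in 1.6% and 2.3% of trials, below its nominal 5%.

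**Step 7. Observation time.** Minimum hours over the 10 infusions (5.6.1, 5.6.2): Pilot 22 + 4 + 2 + 7×1 = 35; Primary 4 + 2 + 8×1 = 14. Of the 21-hour gap, 18 hours fall at Week 0 and the rest at Weeks 4 and 8. From Week 12 the stages are the same.

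**Step 8. Effect of stratifying.** With no drug effect the arms have equal frequencies within each stage, so each stage-specific difference, and any weighted average of them, is zero in expectation. The same holds for Safety Primary alone.

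**The case against.** The strongest reply is that section 8.7 already contains most of the protection. The complete safety analysis is run on the Safety Primary Population, which has 1:1 allocation and one scan schedule. The pooled work is described as more limited, and Pilot data are listed subject by subject. Section 8.1 leaves analysis detail to the SAP, which is not shown and may already split by stage. All of this stands, and it limits the importance of the point. It does not remove it: the treatment-only grouping is a rule that the protocol states, and listings printed beside a crude pooled table do not correct that table.

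It is also fair to object that the scan model is a choice. Independent new findings at a constant rate over ten scans may not hold, and a persistent change visible at any scan would not accumulate. That stands; it is why the range runs down to zero.

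A reader might infer four stronger things that the documents do not support.

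- *That unequal scanning by itself works against GDNF.* It does not; without the change from 2:1 to 1:1 the shift would be zero.
- *That pooled AE frequencies become uninterpretable.* The shift has a ceiling of 8.2 points, is smaller in the scenarios above, and is an expectation whose observed direction is not assured.
- *That Safety Overall supplies the headline safety results.* Section 8.7 gives that role to Safety Primary.
- *That AEs in general are distorted by longer Pilot observation.* The gap is confined to Weeks 0, 4 and 8, and section 7.8 records AEs, including those reported by the participant, from first consent to Week 40 in both stages.

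**Conclusion.** The point holds as a minor one. In the secondary, descriptive Safety Overall tables, the crude between-arm difference in MRI-detected AEs carries an expected shift of 0.0818 × (Pilot rate − Primary rate) with no drug effect. It points towards GDNF if repeated scanning raises detection. Its size is at most 8.2 points, about 1.3 to 4.5 points for assumed per-scan detection of 2% to 10%, and zero without accumulation. In the assumed range it amounts to about one GDNF subject or fewer.

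This rests on 18 + 18 Primary subjects, all 42 dosed as allocated, scheduled scans only, and detection rates that are not in the protocol. The Safety Primary analyses are free of the problem, and the effect on AEs not found by MRI is probably small.

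**What to change.** In section 8.7, and in the SAP and its table shells, state that:

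1. AE tables for the Safety Overall Population are shown by stage within treatment group.
2. Any overall between-arm difference in that set is stratified by stage. A Mantel-Haenszel risk difference is one option; it would weight the Pilot stratum 4×2/6 = 1.33 against 18×18/36 = 9 for the Primary stratum.
3. MRI-detected AEs are compared by arm only in the Safety Primary Population, with Pilot MRI findings reported in the individual listings already planned.

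No scan, visit or observation period changes, and no new subjects or data are needed. Section 8.6 allows revision of the SAP before unblinding. The cost is wording, a rule for which AEs count as MRI-detected, and sparse Pilot columns of 4 and 2 subjects, whose percentages mean little and are better shown as counts.

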## **9 DIRECT ACCESS TO SOURCE DATA/DOCUMENTS**

Direct access will be granted to authorised representatives from the Sponsor, host institution, manufacturer, and the regulatory authorities to permit trial-related monitoring, audits and inspections.

## **10 QUALITY CONTROL AND QUALITY ASSURANCE PROCEDURES**

The study will be conducted in accordance with the current approved protocol, International Conference on Harmonisation (ICH) Good Clinical Practices (GCP), relevant regulations and standard operating procedures.

Regular monitoring will be performed according to ICH GCP. The Sponsor or designee will complete a monitoring plan and provide a copy for the TMF. Data will be evaluated for compliance with the protocol and accuracy in relation to source documents. Following written standard operating procedures, the monitors will verify that the clinical trial is conducted and data are generated, documented and reported in compliance with the protocol, GCP and the applicable regulatory requirements.

The Sponsor or designee will establish an independent DMC. The establishment and operation of the DMC will adhere to relevant guidance, and the responsibilities and processes of the DMC will be specified in a DMC charter.

## 11 SERIOUS BREACHES

The Medicines for Human Use (Clinical Trials) Regulations contain a requirement for the notification of "serious breaches" to the MHRA within 7 days of the Sponsor becoming aware of the breach.

A serious breach is defined as "A breach of GCP or the trial protocol which is likely to affect to a significant degree –

- (a) the safety or physical or mental integrity of the subjects of the trial; or
- (b) the scientific value of the trial."

In the event that a serious breach is suspected NBT R&I should be contacted as soon as possible. Breaches of GCP will be managed in accordance with ISOP-C05

Noncompliance with ICH Good Clinical Practice (GCP) Guidelines

([http://www.nbt.nhs.uk/education\\_research/researcher\\_resources/useful\\_documents\\_forms/standard\\_operating\\_procedures.aspx](http://www.nbt.nhs.uk/education_research/researcher_resources/useful_documents_forms/standard_operating_procedures.aspx))

## **12 ETHICS**

### **12.1 Declaration of Helsinki**

The PI will ensure that this study is conducted in accordance with the principles of the Declaration of Helsinki (as amended by the World Medical Association in Seoul, Republic of Korea, October 2008).

### **12.2 ICH Guidelines for Good Clinical Practice**

The PI will ensure that this study is conducted in full conformity with relevant regulations and with the ICH Guidelines for GCP (CPMP/ICH/135/95) July 1996.

### **12.3 Approvals**

The protocol, informed consent form, participant information sheet and any proposed advertising material will be submitted to the appropriate REC, MHRA, and applicable host institution(s) for written approval.

The PI will submit and, where necessary, obtain approval from the above parties for all substantial amendments to the original approved documents.

### **12.4 Participant Confidentiality**

The trial staff will ensure that the participants' anonymity is maintained. The participants will be identified only by initials and a participant identification number in the CRF and any written study materials. All documents will be stored securely and only accessible by trial staff and authorised personnel. The study will comply with the Data Protection Act which requires data to be anonymised as soon as it is practical to do so.

### **13 DATA HANDLING AND RECORD KEEPING**

Paper CRFs will be used for the current study and a Data Management Plan will be prepared by the Sponsor or designee. The CRF data will be compared to source documentation by the study monitors. All monitored data will be processed by a data management group. Data edit checks will be performed using both CRFs and SAS® programming as detailed in the Data Management Plan. Data queries will be issued to the clinical site in order to resolve any discrepancies found during the discrepancy management process, and data will be updated accordingly. The participants will be identified by a study specific participant number and/or code in any database. The name and any other identifying detail will NOT be included in any study data electronic file.

Previous and concomitant medications will be coded using the latest available World Health Organization (WHO) Drug Reference Dictionary. Coexistent diseases and AEs will be coded using MedDRA.

When the database has been declared to be complete and accurate, it will be locked. Any changes to the database after that time can only be made by written agreement and documented in the TMF.

